#### Coping versatility

The *versatility* subscale of the Coping Flexibility Questionnaire (COFLEX) [51] is used to measure coping versatility.

#### Self-efficacy

To measure self-efficacy for coping with disease symptoms, the Arthritis Self-efficacy Scale (ASES) [30,78]*pain* and *other symptoms* subscales are used.

### Demographics and disease related measures

#### Demographics

Baseline measurement includes demographic variables, including sex, age, marital status, education and current state of employment.

#### Disease characteristics

Diagnosis, disease duration (in years since diagnosis) and number of co-morbidities are asked. The diagnosis is checked by a rheumatologist.

#### Medication use and change of medication

Use of medication is asked with an open-ended question: ‘*What medications do you currently use, as prescribed by your rheumatologist?*’ Furthermore, changes in medication are asked with the question: ‘*Has anything changed in your medication in the past two months?*’ Response options are: ‘*No*’ and ‘*Yes, I started a new drug. / I stopped a drug. / The dose of a drug is increased. / The dose of a drug has been reduced’ .*

### Measures for the economic evaluation

#### Utilities

The EuroQol-5D (EQ-5D) [74,75] is used to assess utilities. The EQ-5D descriptive system consists of five dimensions: mobility, self-care, usual activities, pain/discomfort and anxiety/depression [75]. Furthermore, the ‘thermometer’ is asked; patients rate their health status on a scale from 0 (worst possible health) to 100 (best possible health).

#### Direct medical costs

Medical costs are collected on a bimonthly basis. Patients are asked the number of telephone consultations they have with their GP, as well as their number of visits to the GP, medical specialist, other paramedical and alternative therapists, and hospital days.

#### Indirect non-medical costs

Indirect non-medical costs are collected at the same frequency as the direct medical costs. Patients are asked about their absenteeism from work, domestic care, domestic help, and informal care.

#### Price estimate

Participants in the program group are asked at the post-intervention T1 measurement how many euros they would spend for participation in this program if no health insurance would pay the costs.

### Measures for the process evaluation

A brief questionnaire about the general evaluation of the session, the content, material, exercises and the presentation of the trainer is completed by the participants after each session. The trainers also fill in a short evaluation form at the end of each session and a comprehensive evaluation sheet at the end of each program.

### Measures for the competence of group trainers

During the first two courses, the trainers receive one-hour supervision after every session, and afterwards supervision occurs less frequently, but on a regular basis. Random sessions are recorded with a voice recorder and checked for correct delivery of the protocol.

### Stakeholders’ analysis measures

At the end of a program, two participants per group are randomly chosen and interviewed to evaluate the program with the use of a structured interview scheme. At the end of the study, all the trainers and one person of the management team of the participating clinics are asked during a structured interview to evaluate the program and give suggestions for implementation.

### Sample size

The sample size calculation is based on depressive symptoms as a primary objective. In order to demonstrate a medium-sized effect (Cohen’s *d* = 0.40), 100 participants in each condition are required, based on a statistical power (1-beta) of 0.80, a two-sided test and an alpha of 0.05 (power calculation with G-power).

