### Experimental condition

The program consists of six group-based meetings with 8 to 10 participants and individual homework assignments. “Doelbewust!” is a protocol-based psychosocial educational program. *Doelbewust* is the Dutch word for “purposefully” and we have translated this program name into English as “Right On Target”. The program is led by a trained nurse. Participants are introduced to different goal management strategies and learn to use these strategies to cope in a flexible way with threatened personal goals. The goal management strategies that are covered in the program are: goal maintenance, goal adjustment, goal disengagement, and goal reengagement [39-42].

Table 2 lists the topics, goals, and applied techniques for each meeting of the program. The general structure of each meeting is as follows: a short review of the contents of the previous meeting; introducing the topics of the current meeting; elaborating the topics by group discussions and by practicing in individual, dual and group exercises; and explaining homework assignments for the next meeting. A pilot was executed to test the feasibility of the program protocol.

**Table 2 T2:** Contents of the goal management program

**Meeting**	**Topic**	**Main goals meeting**	**Applied techniques**^**#**^
1.	Arthritis in daily life	Become aware of the influence of polyarthritis in the different domains of life.	Information (general), instruction, problem identification, behavioral information (narratives), modeling (by narratives), vicarious reinforcement (narratives), comparison (with narratives and other participants), emotional social support (by other participants), set homework tasks, prompt (email after meeting to do homework).

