#### Trainers

Specialized nurses in rheumatology care train and support the groups. Participants have the same trainer during the entire intervention period. Before the start of the program, the nurses received a full day ‘train-the-trainer’ course. In this training, the nurses worked through the entire program as a participant and completed the homework assignments to experience the techniques used in the program. In a second phase, the nurses gave the exercises themselves and received detailed feedback on their performance. At the end of the train-the-trainer course, trainers’ knowledge and skills concerning goal management and learned intervention techniques were evaluated. During the study period, trainers receive monitoring and regular supervision by a psychologist.

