### Analysis

#### Preliminary analysis

A flow chart of participation during the total study will be drawn. Reasons for dropout will be summarized. Percentages of missing values and dropout will be displayed. Background variables and summarized scores on questionnaires will be given. One-way ANOVA’S and *χ*^2^-tests will be performed to check for differences between the two conditions at baseline for any of the demographic variables and/or outcome measures. Intention to treat-analyzes will be conducted with use of baseline (T0) or post-intervention (T1) data depending on the last present measurement data.

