#### Effectiveness analysis on primary and secondary outcome measures

To examine differences between the two conditions on all outcome measures, analysis of variance for repeated measures (group x time) will be used. If demographic or outcome measures differ significantly between the groups at baseline, these measures will be incorporated into the analysis as covariate(s). Planned polynomial contrasts are used to analyze differences in effect of the program post-intervention and after the follow-up in the experimental group. Effect sizes of the experimental group in primary and secondary outcomes at post-intervention and follow-up will be calculated with Cohen’s D using the means and pooled standard deviations of the measurements of the conditions. Effect sizes are considered according to Cohen [79] as follows: small d=0.2, medium d=0.5, and large d=0.8. To see if subgroups (e.g., high/low age, gender, disease severity) respond better to the program, subgroup analyzes will be calculated using independent t-tests or Mann–Whitney tests.

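### The experimental arm is treated in course groups of 8 to 10, but the sample size and the group x time ANOVA treat its participants as independent, so the test is anti-conservative if outcomes within a course correlate

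*Protocol article*

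**What the plan says.** On delivery, the protocol article (Experimental condition) states: "The program consists of six group-based meetings with 8 to 10 participants and individual homework assignments". Under Trainers it adds: "Participants have the same trainer during the entire intervention period". Table 2 lists group discussion, social comparison, vicarious reinforcement and emotional support from other participants among the techniques. Under Control condition, waiting-list participants are offered the programme only after the last follow-up, so they belong to no course group while outcomes are collected.

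On sample size, the article sets d = 0.40 and concludes "100 participants in each condition are required, based on a statistical power (1-beta) of 0.80, a two-sided test and an alpha of 0.05". It mentions neither an ICC nor a design effect.

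On analysis, for all outcomes, "analysis of variance for repeated measures (group x time) will be used". In that sentence group means trial condition. Neither course group nor trainer appears in the model. Randomisation is individual and stratified by hospital.

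**The concern.** Members of one course share a nurse and are meant to influence one another, so their post-programme scores may be more alike than those of people from different courses. With 100 participants in groups of 8 to 10, the experimental arm consists of about 10 to 13 courses (100/10 = 10; 100/8 = 12.5). A positive within-course correlation makes the variance of the experimental mean larger than an independent-observations analysis reports. The planned test then rejects too often when there is no effect, on the primary and every secondary between-arm comparison. Stratifying by hospital does not remove this, because courses form within hospitals after randomisation.

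The sample size rests on the same independence, so the 80% does not describe a test that handles the courses correctly.

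**Working it through.** **Inputs from the article:** d = 0.40 (SD set to 1), 100 per arm, 80% power, two-sided alpha 0.05 (Sample size); groups of 8 to 10, taken as m = 9 (Experimental condition); no grouping in the control arm (Control condition).

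**Assumed, because the article gives no figure:** ICC = 0.01, 0.02, 0.05, 0.10.

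**Step 1: reproduce the plan's figure.** The exact two-sample t-test gives 80.4% power at 100 per arm and 79.97% at 99. So 100 is the smallest number per arm that reaches 80% for independent observations, and it holds no reserve for clustering.

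**Step 2: true standard error, clustering in one arm.**
- Design effect in the experimental arm: DE = 1 + (m − 1) × ICC.
- True SE = √[(DE + 1)/100]. Naive SE = √(2/100) = 0.1414.
- Example, ICC 0.05: DE = 1 + 8 × 0.05 = 1.40; SE = √(2.40/100) = 0.1549; ratio to naive = 1.095.

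**Step 3: type I error of the planned (naive) test** = 2 × [1 − Φ(1.96 × 0.1414/SE)].

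**Step 4: power of a test with the correct SE** = Φ(0.40/SE − 1.96). For ICC 0.05: Φ(2.582 − 1.96) = Φ(0.622) = 73%.

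**Step 5: rejection rate of the planned (naive) test at d = 0.40** = Φ[(0.40 − 1.96 × 0.1414)/SE].

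| ICC | DE | SE | Type I, naive test | Power, corrected test | Rejection rate at d = 0.40, naive test |
|---|---|---|---|---|---|
| 0.01 | 1.08 | 0.1442 | 5.5% | 79% | 80% |
| 0.02 | 1.16 | 0.1470 | 5.9% | 78% | 80% |
| 0.05 | 1.40 | 0.1549 | 7.4% | 73% | 79% |
| 0.10 | 1.80 | 0.1673 | 9.8% | 67% | 77% |

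For m = 8 to 10 at ICC 0.05, the type I error runs from 7.1% to 7.7% and corrected power from 74% to 72%.

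**Step 6: detectable effect at 80% power** = 2.80 × SE (1.96 + 0.84). At ICC 0.05, unadjusted: 2.80 × 0.1549 = 0.43.

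**Step 7: with baseline adjustment**, assumed correlation 0.5. Total residual variance falls to 1 − 0.5² = 0.75. Courses form after baseline, so the baseline score does not explain the course variance, which stays at the ICC value.
- ICC 0.05: experimental 0.75 + 8 × 0.05 = 1.15; control 0.75; SE = √(1.90/100) = 0.1378; detectable d = 0.39.
- ICC 0.10: experimental 0.75 + 8 × 0.10 = 1.55; control 0.75; SE = √(2.30/100) = 0.1517; detectable d = 0.42.

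Steps 2 to 7 use the normal distribution. With only 10 to 13 courses, small-sample degrees of freedom lower power a little further.

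**The case against.** **The size depends on a figure the article does not give.** This stands. At ICC 0.01 the consequences are slight (type I error 5.5%, corrected power 79%), and they become material only from about 0.05. A reader might infer that the trial certainly falls short of 80% power. The article does not support that: the shortfall is conditional on the ICC.

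**The power loss and the type I inflation belong to different tests.** This also stands. The planned test, as written, still rejects about 77% to 80% of the time at d = 0.40. Its defect is the false-positive rate. The 73% arises only once the standard errors are corrected, so the two should not be added together as joint harms of one analysis.

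**The planned analysis uses baseline, and the benchmark here does not.** This stands in part. For a change-score contrast the variance per person is 2(1 − r). At an assumed r = 0.6 and ICC 0.05, SE = √[(0.8 + 0.4 + 0.8)/100] = 0.1414 and power is Φ(2.828 − 1.96) = 81%. At r = 0.5 there is no gain (73%). No correlation is stated, so this neither defends the 80% nor establishes a shortfall. It does not repair the standard error either: at r = 0.5, 0.6 and 0.7 the naive-to-true variance is 2.0 to 2.4, 1.6 to 2.0 and 1.2 to 1.6, giving type I errors of 7.4%, 8.0% and 9.0%. A higher baseline correlation makes the relative error worse.

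**Dropout.** A reader might also infer that the sample size assumes no loss, since the analysis section says "Percentages of missing values and dropout will be displayed". The article does not support that. It says "100 participants in each condition are required" without saying that 100 is the number randomised; a recruitment allowance may be in the full protocol, which is not shown. The stated handling carries the last T0 or T1 value forward, so the analysed number need not fall. Dropout forms no part of this point.

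**It could be left to an analysis plan.** This does not stand. The article fixes both a number and a model, and both rest on independence.

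**Conclusion.** The point holds for clustering. Under any positive within-course correlation, the stated ANOVA gives a standard error that is too small and a test that exceeds its nominal 5%. With 9 per group, the type I error is about 5.5% to 9.8% over assumed ICCs of 0.01 to 0.10. Confidence is high that the course group is missing from both the sample size and the model, and lower for the size of the effect, which rests on the assumed ICC.

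As a separate matter, a correctly sized unadjusted comparison with 100 analysed per arm has about 79% to 67% power at d = 0.40 over the same range. At ICC 0.05 its detectable effect is about 0.43. The arithmetic in the Sample size section is right for independent observations; the independence is what does not fit the design. Because grouping is in one arm only, a design effect applied to all 200 participants would overstate the loss.

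**What to change.** **Effectiveness analysis section.** Replace the ANOVA with a partially nested mixed model: a random effect for course group in the experimental arm only, acting on the post-baseline scores, with Satterthwaite or Kenward-Roger degrees of freedom. Include baseline HADS depression as a prespecified covariate for the primary outcome, not one that enters only if the arms differ significantly at baseline. Record each participant's course group in the analysis data.

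**Sample size section.** State an assumed ICC and its basis, and restate the power or detectable effect for 100 analysed per arm. For example: about 73% for d = 0.40 at ICC 0.05 without adjustment, or a detectable d of about 0.39 with baseline adjustment at an assumed correlation of 0.5. Show the less favourable case too (about 0.42 at ICC 0.10 with the same adjustment).

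**Cost.** Course membership and trainer should be known from delivery, so the change is mainly one of wording. Confidence intervals become slightly wider and the unadjusted power statement less favourable. No more patients are needed if the ICC is about 0.05 or less and the baseline correlation about 0.5 or more; beyond that, the restated detectable effect shows what the trial can find.

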### Analysis

#### Preliminary analysis

A flow chart of participation during the total study will be drawn. Reasons for dropout will be summarized. Percentages of missing values and dropout will be displayed. Background variables and summarized scores on questionnaires will be given. One-way ANOVA’S and *χ*^2^-tests will be performed to check for differences between the two conditions at baseline for any of the demographic variables and/or outcome measures. Intention to treat-analyzes will be conducted with use of baseline (T0) or post-intervention (T1) data depending on the last present measurement data.

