### Self-management versus health promotion

The management of most chronic diseases is an extensive responsibility that takes place mostly outside the healthcare system, as people have to manage a chronic disease everyday in combination with possibly conflicting roles and tasks [21]. In fact, the patient, family and community have become active participants in managing chronic disease [22]. Therefore, active self-management and interventions supporting patients in the acquisition of skills and techniques to that help patients learn to live with their disease are seen as essential [23]. A wide variety of self-management interventions has been developed for several chronic conditions. Self-management is ‘*the individuals’ ability to manage the symptoms, treatment, physical and psychosocial consequences and lifestyle changes inherent in living with a chronic condition*’ [24]. Reasonable evidence exists that self-management interventions are beneficial for a wide population of people with chronic diseases, for example, persons with diabetes, hypertension, heart disease and macular degeneration [25,26].

Despite receiving substantial attention in the literature, fewer benefits attained by persons with inflammatory arthritis have been reported [25]. Usually the effects of self-management interventions found for people with inflammatory arthritis are negligible to small [23,27]. Also, improvements are rarely sustained over a longer time (e.g., 9 to 14 months follow-up) [27-29]. The aforementioned term ‘self-management’ is used in literature to describe both health-oriented and disease management interventions [26], and this may cause confusion regarding the content and focus of interventions. The most frequently offered and studied self-management program for people with arthritis is the Arthritis Self-Management Course [30,31], in which common problems with day-to-day care of arthritis patients are central.

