## Methods and design

### Participants

The study has been approved by the medical ethics committee Twente, number NL40257.044.12. Participants are recruited via arthritis clinics in four general hospitals in The Netherlands, located in the East and Southeast areas of the country. Moreover, people from existing databases of research participants are invited to participate. Also local newspapers and contacts with patient organizations are used to reach potential participants. The process for obtaining participant informed consent is in accordance with all applicable regulatory requirements.

The research population consists of people with polyarthritis (as defined by the DBC classification system) with a psychological risk profile. The specific inclusion criteria are: 1) age of 18 years or over, 2) diagnosis of polyarthritis, and 3) score of four or higher on the depression subscale of the Hospital Anxiety and Depression Scale (HADS). People with severe distress are excluded and the treating rheumatologist is informed. Severe distress is measured as a total score on the HADS (the total of both the depression and anxiety subscales) of 22 or higher. The cut-off score is based on literature [59,60]. In addition, insufficient Dutch language skills and actual enrolment in psychotherapeutic treatment at the moment of study are exclusion criteria.

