### Control condition

Participants in the waiting list condition do not receive the “Right On Target” program immediately. Eight months after entry into the study, which is directly after the last follow-up measurement, participants on the waiting list are invited to follow the program.

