### Measurements

Table 3 gives an overview of the properties of the measurement instruments used. Participants are asked to complete six questionnaires including: intake, baseline (T0), directly after the end of the program (T1), 2 months after the end of the program (T2), 4 months after the end of the program (T3), and 6 months after the end of the program (T4). Nearly all the instruments listed in Table 3 were applied in a previous study with polyarthritis patients [12], and, when available, Cronbach’s alphas from that previous study also appear in Table 3.

**Table 3 T3:** Study parameters, properties of the corresponding instruments and their measurement point(s)

**Content**	**Measurement point**	**Scale**	**Reference**	**Example item**	**Scale range**	**Cronbach’s alpha **^**a**^	**Items**	**Response options**
Depression	Intake, T0, T1, T4	Hospital Anxiety and Depression Scale (HADS)	Zigmond & Snaith, 1983 [60]	I have lost interest in my appearance.	0-21	.81	7	various response format (0–3)
Anxiety	Intake, T0, T1, T4	HADS	Zigmond & Snaith, 1983	I feel tense or wound up.	0-21	.83	7	various response format (0–3)
Positive affect	T0, T1, T4	Positive subscale of the Positive and Negative Affect Schedule (PANAS)	Watson, Clark, & Tellegen, 1988 [67]	Rate how you felt during the past week: e.g., *attentive*, *interested*.	10-50	.92	10	very slightly or not at all (1) - very much (5)
Purpose in life	T0, T1, T4	Purpose In Life scale (PIL)	Ryff, 1989 [68]; Ryff & Keyes, 1995 [69]	My daily activities often seem trivial and unimportant to me.	6-30	.82	6	strongly disagree (1) -strongly agree (5)
Social participation	T0, T1, T4	Family role, autonomy outdoors, social relations and work and education subscales of the Impact on Participation and Autonomy (IPA) questionnaire	Cardol, De Haan, De Jong, Van den Bos, & De Groot, 2001 [70]	Domain autonomy outdoors: The possibility to spend my (spare) time like I want to is…	0-4	.76	25	very good (0) - very poor (4)
Pain	T0, T1, T4	1 item with 100 mm visual analogue scale	-	Please indicate how much pain you had in the last 7 days due to your condition?	0-100	-	1	no pain at all (0) -unbearable pain (100)
Fatigue	T0, T1, T4	1 item with 100 mm visual analogue scale	-	Please indicate your level of fatigue averaged over the past 7 days?	0-100	-	1	no fatigue (0) -completely exhausted (100)

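### Carrying T0 or T1 forward as the intention-to-treat rule can bias the T1 and T4 effects in either direction; an analysis of the observed data should replace it

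*Protocol article*

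**What the plan says.** The Preliminary analysis section of the Protocol article fixes the handling of missing outcomes in one sentence: "Intention to treat-analyzes will be conducted with use of baseline (T0) or post-intervention (T1) data depending on the last present measurement data". Table 3 (Measurements) gives the time points for HADS depression, the primary outcome, as "Intake, T0, T1, T4". Taken together, a missing T4 is filled with T1, or with T0 if T1 is missing too, and a missing T1 is filled with T0.

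The section on effectiveness analysis then says that "analysis of variance for repeated measures (group x time) will be used", and that effect sizes at post-intervention and follow-up "will be calculated with Cohen’s D using the means and pooled standard deviations of the measurements of the conditions". It also plans contrasts of post-intervention with follow-up within the experimental group. The article names no other missing-data method.

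Two further places bear on the point. The background says of self-management programmes for inflammatory arthritis that "improvements are rarely sustained over a longer time". The Control condition section invites waiting-list participants to the programme at a set time: "Eight months after entry into the study, which is directly after the last follow-up measurement".

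**The concern.** Carry-forward replaces an unknown later score by an earlier one. That is harmless only if the score would not have moved, or if the resulting errors are equal in both arms. Neither is a safe assumption here.

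- **T1 carried to T4.** This assumes that any benefit at the end of the programme is still fully present six months later. Durability is one of the things the follow-up and the planned contrasts are meant to test, and the background says it is uncommon in this field.
- **T0 carried to T1 or T4.** This assumes no change at all. The programme is meant to change scores. Participants are also selected on a HADS depression score of at least 4 at intake, so some regression to the mean is plausible in both arms, although part of it may already have occurred by T0.
- **Unequal dropout.** The trial is open label. One arm attends six meetings with homework, and the other is offered the programme after its last measurement. Different dropout by arm is therefore plausible, and any common drift in scores would then turn into a difference between groups.

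At stake are the estimates of the primary outcome at both post-baseline time points and, in some circumstances, the false-positive rate.

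**Working it through.** **Plan's own figure.** For d = 0.40, two-sided alpha 0.05 and power 0.80, the normal approximation gives 99 per arm and the t-test gives 99.08, rounded up to 100, with power 0.804. The stated 100 per condition is reproduced and is not in dispute.

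**Inputs.** From the article: effect 0.40 SD, 100 per arm, measurements at T0, T1 and T4. Assumed, because the article gives none: dropout of 10% to 30%, the fading of the effect, and natural change in scores. Effects are in SD units, and dropout is taken as unrelated to the scores. The simulations used 100 per arm, an assumed within-person correlation of 0.6, 4,000 replicates and a t-test on change from T0 to T4. That test is a simplification of the planned group-by-time analysis.

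**1. T1 carried to T4, fading effect.** With share p missing T4 in both arms:

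reported T4 effect = (1 − p) × e4 + p × e1

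- e1 = 0.40, e4 = 0.20, p = 20%: 0.8 × 0.20 + 0.2 × 0.40 = **0.24** (0.22 at 10%, 0.26 at 30%).
- e1 = 0.40, e4 = 0.10, p = 20%: 0.8 × 0.10 + 0.2 × 0.40 = **0.16** (0.19 at 30%).

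**2. T0 carried to T1.** With true effect δ, natural improvement g, and dropout dE (experimental) and dC (control):

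reported T1 effect = (1 − dE)(δ + g) − (1 − dC) × g

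- δ = 0.40, g = 0.2, dE = 20%, dC = 10%: 0.80 × 0.60 − 0.90 × 0.20 = 0.48 − 0.18 = **0.30**. A simulation gave 0.302.
- Equal dropout: 0.40 × (1 − d) = 0.36, 0.32 and 0.28 at 10%, 20% and 30%. Observed cases stay at 0.40 under the same dropout.

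**3. No effect, common drift, unequal dropout before T1.** With δ = 0 the formula reduces to (dC − dE) × g.

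- dE = 30%, dC = 10%, g = 0.4 by T4: (0.10 − 0.30) × 0.4 = −0.08. If scores improve, the error goes against the programme. If they worsen, it favours the programme.
- Simulated bias was −0.079 and +0.081. Type I error was **0.105** and **0.114**, against 0.05 for observed cases.

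**4. Conditions under which the rule does no harm.**

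- Durable effect of 0.40 and 20% dropout only after T1: simulated T4 effect 0.402.
- No effect and no change over time: type I error 0.049 with equal 20% dropout, 0.054 with 10% against 30%.

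**The case against.** The strongest reply is that nothing in the article says dropout will be large, unequal, or followed by change. This stands as far as size is concerned. With a milder set of assumptions (no effect, 0.2 SD drift, 20% against 10% dropout) the simulated bias is 0.017 SD and type I error 0.052. The background remark on poor durability concerns self-management programmes, from which the authors distinguish theirs. It makes fading plausible but gives no amount. The article also commits to reporting a flow chart, dropout reasons and missing percentages, so an imbalance would be seen, although not corrected.

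A reader might infer three stronger things that the documents do not support.

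- **That carry-forward costs power, from 80% to 67%.** With equal 15% dropout the effect becomes 0.85 × 0.40 = 0.34, and a t-test on T1 scores then has power 0.667. But the planned analysis rests on change over time. Carried-forward T0 values give zero change, which shrinks the variance along with the effect. On change scores, power was the same with carry-forward as with observed cases: 0.75, 0.82 and 0.92 at correlations 0.5, 0.6 and 0.7. Even on T1 scores alone, 85 observed per arm would give 74%, so much of the apparent loss is ordinary loss of data.
- **That the standard error is understated.** Each filled value comes from the same participant, so participants remain independent. In simulation the mean standard error and the sampling SD of the estimate were both 0.117. The raised type I error in step 3 comes from bias.
- **That the rule favours the programme.** The direction depends on when participants leave, from which arm, and how scores move.

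A last objection is that the remedy also changes the analysis model. It does, for a practical reason: conventional repeated-measures ANOVA needs complete records, so dropping carry-forward requires a method that accepts incomplete ones.

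**Conclusion.** The point holds as one of bias. The article itself fixes single carry-forward as its intention-to-treat rule, so this is not a detail left to an analysis plan. The rule distorts the T1 and T4 effects, in either direction, when scores would have changed after dropout and the changes do not cancel between arms. Under the assumptions shown, the error is 0.04 to 0.06 SD at T4 for a fading effect with 20% missing, and 0.10 SD at T1 with 20% against 10% dropout and 0.2 SD natural improvement. Type I error reaches about 0.10 only with both marked imbalance (30% against 10%) and a 0.4 SD drift. It is about nil with a durable effect and dropout only after T1.

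Because dropout and change over time are unknown, the documents do not show that the trial's conclusion would be wrong. This should be fixed, but it is not shown to be indispensable.

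**What to change.** Replace the sentence in Preliminary analysis with: *All randomised participants are analysed as allocated in a likelihood-based mixed model for repeated measures using every observed T0, T1 and T4 value, with no single imputation.* The effectiveness section should be brought into line: the group-by-time comparison stays, fitted by this model, and effect sizes should not be computed from filled-in values.

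Add one sensitivity analysis for data missing not at random, for example multiple imputation with a delta shift for dropouts. Carry-forward may stay only as a labelled sensitivity analysis.

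The cost is a change of wording and a little more analysis work, with no new data, visits or participants. The downside is that the primary analysis then relies on data being missing at random, which the sensitivity analysis is there to test.
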